**Primary outcome**								
	**Complication rate, defined as the occurrence of at least 1 of the following events within 6 months of trauma [42]:**			Clinical and claims data			6 months	
		Occurrence of pseudarthrosis (incomplete fracture healing)	Clinical data			6 months		
		Occurrence of chronic osteomyelitis	Clinical data			6 months		
		Unplanned follow-up procedures, such as wound revisions and NPWT^a^	Clinical and claims data			6 months		
		Deviation from standardized antibiotic therapy (extension of the duration of therapy or change or expansion of the active substance)	Clinical and claims data			6 months		
		Occurrence of antibiotic-associated complications (eg, clostridia infection or allergy)	Clinical and claims data			6 months		
		Infection with resistant germs (eg, MRSA^b^) that occurred during inpatient treatment and did not exist at the time of trauma [43]	Clinical data			6 months		
		Need for unplanned inpatient treatment	Clinical and claims data			6 months		
		Death of the patient related to the trauma (not due to other causes)	Clinical and claims data			6 months		

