## Introduction

### Background

Open fractures of the lower extremities are common, occurring with an incidence of approximately 11.5 per 100,000 [1]. Patients with open fractures often experience complications in the course of the disease, such as soft tissue infections, bone inflammation, defective bone fuse, and increased tissue pressure around the injury, with negative effects on blood supply and the nervous system [2,3]. Even for highly experienced service providers, it is often not possible to provide a sufficient quality of care for disciplines such as trauma, vascular and plastic surgery, infectiology, microbiology, and hygiene [4]. However, such interdisciplinary treatment has not yet been established in German primary and standard care. Currently, many patients with complicated or incorrectly healed fractures, infections, or chronically open wounds see several physicians in different hospitals, combined with inpatient transfers, redundant diagnostics, and long sick leave [5-7]. In many cases, the healing process is significantly impaired, and it is not uncommon for serious restrictions to remain.

In addition to the physical and psychological consequences for those affected, there are also the considerable costs of the health care system [1,8,9]. Patients with open lower-leg fractures incur almost twice as much cost (€11,000 [US $12,000]) as patients with closed fractures (€6600 [US $7100]) [5]. Open fractures with soft tissue infections lead to increased antibiotic use, additional surgeries, and longer hospital stays, which can increase costs 6-fold [5,10,11]. Against the backdrop of demographic change [12,13] as well as the increasing incidence of fractures due to comorbidities (eg, osteoporosis, gait uncertainty, and neurological diseases) and complications in the healing process from the age of 65 years onward, improving treatment options for complicated fractures and reducing the complication rate are of extreme importance [14]. Main complications that are encountered in this context are pseudarthrosis and chronic osteomyelitis. Pseudarthrosis is defined as a problem in fracture healing with missing consolidation of >6 months after trauma. Chronic osteomyelitis is a state in which destructive changes within the bone occur due to an infectious process. Both conditions prolong the healing process and usually make several surgical procedures necessary. In some cases, even an amputation must be considered.

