## Methods

### Study Design

#### Clinical and Health Economic Evaluation

For the organization and evaluation of the new form of care, a stepped-wedge design was chosen [36,37]. In a stepped-wedge design, there are different clusters that start recruitment at the same time in the control phase. The individual clusters then move gradually into the intervention phase in randomized cohorts. In the EXPERT project, there is a transition phase between the control and intervention periods, which serves to implement and test the new form of care in the individual clinics as well as train the staff.

Randomization in the EXPERT project will take place at the hospital level. There are 31 hospitals participating in the study. Each clinic forms a cluster that belongs to 1 of 4 cohorts. The clusters within a cohort always enter the next study phase (transition or intervention phase) at the same time. The study will be conducted over a period of 24 months (18-month recruitment period+6-month follow-up of the last enrolled person). Data collection regarding the individual course of treatment takes place from the time of enrollment in the patient sample until 6 months later. Figure 2 shows the planned course of the study in the stepped-wedge design.

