**Clinical criteria**
Inclusion criteriaPatients who meet at least one of the following 2 criteria: fractures of the extremities with open soft tissue damage (according to Gustilo et al [41]) OR postoperative complications (according to the criteria of the Association of the Study of Internal Fixation Anti-Infection Task Force) or unplanned reoperation within 6 months of initial surgery; these criteria are operationalized via the *International Statistical Classification of Diseases and Related Health Problems, 10th Revision*, codes for the following: open soft tissue damage in fractures or dislocations as well as amputations of the lower extremities; infections of the lower extremities (excluding joints and joint arthroplasty); infections of joints or joint endoprostheses of the lower extremities; pseudarthrosis and delayed fracture healing of the lower extremitiesExclusion criteriaPatients who meet both of the following criteria: no fracture of the extremities or closed fracture of the extremities without open soft tissue damage AND no postoperative complication or unplanned reoperation within 6 months of initial surgery

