### Outcomes and Measures

#### Clinical and Health Economic Evaluation

The primary outcome and various secondary clinical outcomes are recorded based on data from the clinical case file as well as routine data from the health insurance companies.

The primary clinical outcome is the complication rate of open fractures or the occurrence of postoperative complications, which is collectively defined as a dichotomous outcome. Either the occurrence or nonoccurrence of complications is observed. The following events are complications if they occur within 6 months of enrollment in the sample: (1) occurrence of pseudarthrosis (incomplete fracture healing; *ICD-10* code M96.0); (2) occurrence of chronic osteomyelitis (*ICD-10* code M86.69); (3) unplanned follow-up procedures, such as wound revisions and Negative Pressure Wound Therapy (*ICD-10* code S81.801); (4) deviation from standardized antibiotic therapy (extension of the duration of therapy or change or expansion of the active substance; *ICD-10* code T36.95); (5) occurrence of antibiotic-associated complications (eg, clostridia infection or allergy; *ICD-10* code B96.7); (6) infection with resistant germs (eg, methicillin-resistant *Staphylococcus aureus*) that occurred during inpatient treatment and did not exist at the time of trauma (*ICD-10* code A49.02); (7) need for unplanned inpatient treatment; and (8) death of the patient related to the trauma (not due to other causes).

Secondary clinical outcomes include the number of antibiotics administered, limb function, and health-related quality of life (HRQoL) [44,45].

Health economic outcomes are mapped through claims data from health insurance companies. These will be recorded for each patient included in the project up to 6 months after enrollment in the sample. Specifically, the following features will be recorded: (1) use of health services (eg, contact with physicians and therapists, operations, and inpatient stays), (2) cost of health care services (inpatient hospital costs, outpatient costs, rehabilitation costs, medical and medical aid costs, drug costs, and total costs), (3) number of days on which there is incapacity for work, and (4) number of days on which sickness benefits are received.

Table 1 provides an overview of the clinical and health economic outcomes used in this study.

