### Data Analysis

#### Clinical and Health Economic Evaluation

The eligible patients are enrolled in the project by trained staff. Patients are informed about the objectives and course of the project and give their written consent to participate. Each case is summarized with all relevant information (eg, anamnesis, findings, and imaging) in a clinical case file using data-secure web-based software. The case files are checked for completeness and, after approval, transmitted digitally to the interdisciplinary expert group, the Extremity Board. This group of experts is recruited from the following disciplines: trauma surgery, plastic surgery, vascular surgery, radiology, angiology, and antibiotic stewardship (microbiology, hygiene, infectiology, and pharmacy) [43]. The experts meet at least weekly via web conference and, depending on the urgency, discuss the cases together. Agreed interdisciplinary therapy recommendations are written and transmitted back to the presenting clinic via the web-based software platform. In addition, guidelines will be defined in the course of the project on the basis of the findings gained by the Board to objectify decision-making paths, streamline processes, define therapy algorithms, and enable the supraregional applicability of these standards.

The clinical case files of all patients included in the EXPERT project will be merged with the respective patient-related health insurance data in an anonymized data file for each case while maintaining data protection. Claims data from health insurance companies provide information about the use of health services and the costs that arise in doing so. To obtain information about the individual course of treatment after the introduction of the new form of care, claims data for the following 6 months are included in the evaluation for each patient from the time of enrollment in the sample. Thus, the clinical case file and the associated health insurance data depict the course of treatment of a patient, which is included in the evaluation.

To be able to evaluate the extent to which the new care measures improve the chances of recovery and reduce costs, various clinical and economic outcomes are collected.

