### Strengths and Limitations

When measuring the quality of treatment in trauma surgery, several influencing factors must be considered. The type of injury, the extent of anatomical reconstruction during surgery, soft tissue management, perioperative management, and rehabilitation protocols as well as patient compliance have a major influence on the outcome and make evaluation difficult. For our study, we chose 4 outcome measures: the complication rate after initial surgery (nonunion, infection, unplanned surgical revision, and need for prolonged antibiotic therapy), the number of applied antibiotics, the functionality of the injured limb, and HRQoL.

The clinical outcome is examined using a stepped-wedge design, which allows for the statistical consideration of time effects. The design also has practical advantages, such as the easy implementation of a staggered rollout. Among the weaknesses of a stepped-wedge design are time-sensitive recruitment efforts, complex randomization requirements when assigning hospitals to different cohorts or wedges, the assumption of high treatment schedule fidelity, and effects of the observation (the so-called Hawthorne effect) [74].

We choose a difference-in-difference design, a widely used quasi-experimental design in clinical research, to evaluate work-related outcomes. This design eliminates confounding by comparing outcomes before and after treatment. However, the design relies on a parallel-slopes assumption, which is hard to manage and may not always apply [75].

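### The primary composite cannot be scored unambiguously: its 6-month window runs from enrollment in the text but from trauma in Table 1, and pseudarthrosis as defined fits neither window for a patient enrolled at injury

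*Protocol article*

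**What the plan says.** The primary outcome is dichotomous: a patient has the event if any of eight components occurs. The protocol article dates the window in two ways.

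- Methods, Outcomes and Measures (text): "The following events are complications if they occur within 6 months of enrollment in the sample".
- Table 1, Primary outcome: "defined as the occurrence of at least 1 of the following events within 6 months of trauma".

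The data are gathered on the enrollment clock. Under Study Design: "Data collection regarding the individual course of treatment takes place from the time of enrollment in the patient sample until 6 months later". Under Data Analysis: "claims data for the following 6 months are included in the evaluation for each patient from the time of enrollment in the sample".

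Enrollment need not coincide with injury. Besides open fractures, Textbox 2 (Clinical criteria) admits patients with postoperative complications or "unplanned reoperation within 6 months of initial surgery". It also lists pseudarthrosis and delayed healing among the diagnoses that operationalize entry. Unplanned follow-up procedures and pseudarthrosis are therefore both routes into the trial and components of the outcome.

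The first component in Table 1 is "Occurrence of pseudarthrosis (incomplete fracture healing"), taken from clinical data at 6 months. The Background section states: "Pseudarthrosis is defined as a problem in fracture healing with missing consolidation of >6 months after trauma".

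**The concern.** For a patient enrolled on the day of injury the two windows are the same. For a patient enrolled later they are not, and the article admits such patients by design. The same patient can then be an event under one definition and a non-event under the other, so two analysts could report different primary results from the same records.

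Table 1's window creates two specific problems for late entrants. It shortens the time in which a post-enrollment complication can count. It also reaches back before enrollment, so that the reoperation or complication that made the patient eligible falls inside the outcome window. The board could not have prevented that event, and in a stepped-wedge trial it may have happened in an earlier phase than the one in which the patient is analyzed. Neither definition says that the qualifying event is left out. Only the resistant-germ component excludes a pre-existing condition, and it does so relative to trauma, not enrollment.

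The pseudarthrosis component raises a separate question: whether a condition defined as lasting more than 6 months from trauma can be observed within a 6-month window at all.

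**Working it through.** **The plan's own figure.** The planning rates are 40% and 30%, a 10-point difference, with α = 5%, power 80%, intraclass correlation 0.05 and 17 patients per hospital per 3-month interval. Assuming a two-sided test, individual randomization needs 356 per arm, or 712. The stepped-wedge design effect, assuming 4 steps and 2 baseline intervals, is

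[1 + 0.05(68 + 34 − 1)] / [1 + 0.05(34 + 34 − 1)] × 3(0.95) / [2(4 − 1/4)] = (6.05 / 4.35) × 0.38 = 0.529.

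Then 712 × 0.529 × 6 ≈ 2258, and 2258 / 0.8 / (5/6) ≈ 3387, within 0.6% of the stated 3366. The figure uses neither window, so it does not show which one was intended.

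**The two windows.** Let L be the months from trauma to enrollment.

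- Trauma window (Table 1): closes 6 months after trauma, leaving max(0, 6 − L) months at risk after enrollment.
- Enrollment window (text): always 6 months at risk, closing 6 + L months after trauma.
- Pseudarthrosis by the Background definition can first be met after month 6 from trauma. That leaves 0 months of opportunity under the trauma window and L months under the enrollment window.

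| L | Months at risk after enrollment, Table 1 | Months at risk, text | Months in which pseudarthrosis can be met, Table 1 | Same, text |
|---|---|---|---|---|
| 0 | 6 | 6 | 0 | 0 |
| 1 | 5 | 6 | 0 | 1 |
| 3 | 3 | 6 | 0 | 3 |
| 6 | 0 | 6 | 0 | 6 |

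The L values are illustrative; the article gives no distribution of this lag.

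**A worked case.** Take a patient operated on soon after injury, who has an unplanned reoperation at month 3, is enrolled then on that ground, and has no further event. Under Table 1 the reoperation lies within 6 months of trauma and scores as an unplanned follow-up procedure: event. Under the text, counting what occurs after enrollment: no event. If the same patient instead has a new wound revision at month 8, the text counts it (month 5 after enrollment). The trauma window, which closed at month 6, does not.

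**What counting qualifying events would do (illustration only).** Suppose a share s of patients is event-positive at entry in both phases. The rates become s + (1 − s) × 0.40 and s + (1 − s) × 0.30, so the difference is 10(1 − s) points:

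- s = 0.1: 46% vs 37%, 9 points
- s = 0.3: 58% vs 51%, 7 points
- s = 0.5: 70% vs 65%, 5 points

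The documents do not give s, and the calculation applies only if qualifying events are counted.

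**The case against.** The strongest reply is that enrollment is plainly the working clock. Data collection, the outcome text, the health economic outcomes, the quality-of-life assessments and the claims window all run from it, and the text introduces Table 1 only as an overview. On that view, trauma in Table 1 is one stray word, and events occurring within 6 months of enrollment naturally means new events. This stands as a reason for choosing enrollment. It does not remove the conflict, because Table 1 is where the composite rule of at least one event is set out in full, and nothing says which statement governs.

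A second reply is that Table 1 describes pseudarthrosis as incomplete healing assessed from clinical data at 6 months, which can be observed. That is fair, and it points to the remedy. It still has to be squared with the Background definition.

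Several stronger readings are tempting but not supported:

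- *That the outcome cannot be scored at all.* The other seven components can be scored once one window is chosen.
- *That there is a third time origin.* The Discussion speaks of "the complication rate after initial surgery (nonunion, infection, unplanned surgical revision, and need for prolonged antibiotic therapy"), but this is a summary that sets no window.
- *That pseudarthrosis present at entry counts as an event under Table 1.* By the Background definition it arises after that window has closed.
- *That pseudarthrosis is unobservable in most patients, or that most of the window predates enrollment.* Neither the entry mix nor the lag is given.
- *That the required sample size grows by a known factor.* Any such factor would come from the assumed s.
- *That the antibiotic component is scored against a different standard in each phase.* The article says guidelines will be developed during the project, but not that the reference for this component changes with phase.

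**Conclusion.** The point holds as an internal contradiction in the primary endpoint. The text and Table 1 give different 6-month windows, and they diverge for patients whom the entry criteria expressly admit. Under Table 1 the time at risk after enrollment falls to 6 − L months, and a qualifying complication or reoperation that preceded enrollment would score as the outcome. Pseudarthrosis, taken as the Background defines it, can never be met under Table 1. Under the enrollment window it cannot be met by a patient enrolled at injury.

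The effect on the planned 40% and 30% cannot be computed, because the article gives neither the lag from trauma to enrollment, nor the share entering through a complication or reoperation, nor the component rates. The shrinkage to 10(1 − s) points shows the direction of the risk if qualifying events are counted. It is not an estimate for this trial.

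Because the choice of window can change individual patients' primary outcomes, it should be settled before outcomes are analyzed.

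**What to change.** 1. In Table 1, replace trauma with enrollment as the start of the 6-month window, so that it agrees with the text, data collection and the claims window.
2. State in both places that only events beginning after enrollment, and distinct from the condition that qualified the patient, count toward the composite.
3. Reconcile the pseudarthrosis component with the Background definition, for example by scoring it as incomplete fracture healing (non-consolidation) at the existing 6-month assessment. This keeps the present follow-up and data source.
4. Optionally, add entry route (open fracture versus complication or reoperation) as a covariate. The analysis section already plans adjustment for patient and trauma factors.

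Items 1 to 3 are changes of wording and scoring rules. They need no added follow-up or patients. Item 4 uses information already needed to establish eligibility.

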**Secondary clinical outcomes**								
	Number of antibiotics administered			Clinical and claims data			6 months	
	Limb function			Clinical data			6 months	
	HRQoL^c^, measured using the VR-36^d^ [44] and EQ-5D [45,46]			Clinical data			0 and 6 months	
**Health economic outcomes**								
	Use of health care services			Claims data			6 months	
	Cost of health care services			Claims data			6 months	
	Days of incapacity for work			Claims data			6 months	
	Sickness benefit days			Claims data			6 months	

^a^NPWT: negative pressure wound therapy.

^b^MRSA: methicillin-resistant *Staphylococcus aureus*.

^c^HRQoL: health-related quality of life.

^d^VR-36: Veterans RAND 36-item Health Survey.

#### Work-Related Evaluation

##### Questionnaires

Building on experiences and results from previous ergonomics studies in the fields of medical care and outpatient and inpatient care [47-49] and using the JD-R model as a theoretical frame of reference, the work-related evaluation uses validated measurement tools that measure workload, work engagement, work-related resources, and technological readiness. As the new form of care in the EXPERT project requires a competent application of telemedical technology, ergonomic aspects of the new telemedicine application are also recorded. The 7 items for the usability of the telemedicine application are only administered to the treatment group at the second measurement time. Therefore, the EXPERT questionnaire comprises 4 instruments with 31 items without ergonomic aspects and 5 instruments with 38 items with ergonomic aspects. Empirical comparative values are available for all measuring instruments used.

Workload is measured using the National Aeronautics and Space Administration Task Load Index [50] in a version for teamwork [51,52]. For this study, an abridged version of this questionnaire with 8 items in the German translation is used. On a scale of 1 to 10 (1=*very low*; 10=*very high*), employees estimate the mental, time, and performance-related work requirements as well as the effort regarding exchange, organization of work, team effectiveness, and mutual support for the past 3 months and give an assessment of their satisfaction with the cooperation. For example, a formulation is “How much effort was required to organize the work (e.g., coordination of who takes on which task, when which task is completed)?”

Work engagement is measured using the ultra–short form of the Utrecht Work Engagement Scale, which contains 3 items [53]. The German translations of “At work I am full of energy,” “I am enthusiastic about my work,” and “I am completely absorbed in my work” are used, which are rated on a scale from 0 to 6 (0=*never*; 6=*always*).

Work resources are measured using the German-language questionnaire on resources and requirements in the world of work [54]. For the EXPERT project, 11 items are used, which relate to the resources “Leadership Support,” “Feedback,” “Peer-Support,” “Transparency,” “Diversity,” “Meaningfulness,” “Role Clarity,” “Learning Opportunity,” “Knowledge Management,” “Team Atmosphere,” and “Qualification.” All items are formulated as statements (eg, “I will be informed about all important content when implementing the new measures” [“transparency” resource]), which are rated on a scale from 1 to 6 (1=*not at all true*; 6=*completely true*).

Affinity for technology is measured using the German-language short scale for measuring readiness for technology [55]. It is a questionnaire with 12 items in the 3 scales “TB acceptance,” “TB control belief,” and “TB competence,” of which 9 items are used in this study. The item formulations have been adapted to the EXPERT project (eg, “I am very interested in the new telemedicine application” [acceptance scale], “It essentially depends on me whether I am successful in using the new telemedicine application” [control conviction scale], and “For me, dealing with technical innovations is usually too much to handle” [competence scale]).

The software ergonomics of the new telemedicine application are assessed using the German-language questionnaire Norm of the International Standard Organization 9241/10 [56,57]. On the basis of this instrument, software is evaluated regarding “adaptivity to requirements,” “comprehensibility,” “task appropriateness,” “ability to describe itself,” “fault tolerance,” “individualizable,” and “learning conduciveness.” The assessment of the 7 items is made on a bipolar scale based on symbols (from “– – –” to “+++”).

Finally, employees provide information about their profession (physician or nurse), whether they hold a management position (yes or no), and whether they already had experience in the use of telemedicine before the EXPERT project (yes or no).

